**Table 4 Tab4:** **Classification of disease severity**

**Classification**	**Features**
**1. Mild**	Can continue to participate in the clinical trial, without obstacles in the activities of daily living
**2. Moderate**	Has certain obstacles to daily life, but not to the point of completely diminished function
**3. Severe**	The extent of obstacles in the activities of daily living has led to the risk of permanent disability, and appropriate measures are needed to mitigate medical issues

**Table 5 Tab5:** **Classification of adverse events**

**Classification**	**Feature**
**1. Definite**	Use of the experimental drug has a definite relationship with time.
	Similar pharmacologic effects of the drug or experimental drug are well known.
	There is no other plausible cause owing to disease or other explanations.
**2. Probable**	Use of the experimental drug has a reasonable relationship with time.
	Similar pharmacologic effects of the drug or experimental drug are well known.
	It is difficult to identify a cause owing to disease or other explanations.
**3. Possible**	Use of the experimental drug has a reasonable relationship with time.
	The adverse event may be caused by disease or other explanations.
**4. Remote**	There is a connection between time and test drug.
	It is easy to explain through disease or the main causes of a disease.
**5. Unrelated**	There is no connection between time and the test drug.
	The adverse event is definitely caused by other reasons, and not the test drug.

### Data management

#### Management of the analyses of data entry by a third party (Southern Medical University, China)

Management of the data entry and analyses will be undertaken by a specific data manager responsible for building the study database and program settings. Data will be inputted twice and confirmed by two keyboard operators who have received special training. After verification of the case report forms (CRFs), identified input errors will be corrected until there are no differences in the database. Uncertainties can be discussed with the researcher using CRF question forms. These question forms shall be completed by the researcher within a specified time limit as well as being signed and dated. Completed question forms will be sent to the Department Of Database Management. The data manager will revise and verify the feedback from the researcher, update the database, and resend the form (if necessary). After confirming the veracity of the database *via* blind review, locked data will not be corrected. Data revision after locking will be confirmed by the study promoters, researchers, program manager, statistician, and the data manager with a written declaration and will be corrected in the statistical analyses. After data review, all cases will be evaluated by confirming the intent-to-treat population (ITTP), modified intent-to-treat population (MITTP), per-protocol population (PPP) and safety analysis population (SAP). The decision will be approved by the data manager, study promoter, and researchers, and will end with unblinding after locking the database.

#### Patient groups for data analyses

##### Intent-to-treat population

The intent-to treat population will include those patients who agree to enroll in the study and sign an informed consent form.

##### Modified intent-to-treat population

The modified intent-to-treat population includes those patients who used the test drug at least once during randomization, and data will be used to indicate efficacy after intervention.

##### Per protocol population

The per protocol population includes those cases that meet the inclusion criteria, are in full accordance with the test program (or violate the protocol only slightly), complete the trial and complete the CRF. The PP is used to analyze the main indicators for evaluating efficacy and to examine the consistency of the results from the MITT.

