### Design

This clinical study was a randomized, double-blind, double control trial that tested drugs and placebo. Noninferiority (versus positive control) and superiority (versus placebo control) trials were conducted. Patients with positive tests for the influenza virus (rapid detection of antigens to the influenza virus before enrollment, but if detection of nucleic acid of the influenza virus or cultivation of the influenza virus was inconsistent, the patient was excluded) were assigned randomly into three groups of equal proportions (1:1:1). Groups were: oseltamivir treatment (positive control), BLG granule treatment (test group) and placebo group. Patients will accept 5-day treatment and 21-day observation. Patient follow-up was undertaken on days 1, 3, 5, 7, 21 (Table 1 and Figure 1). Specific items that were collected for each follow-up period are outlined in Table 1.

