### Number of participants and specimen collection

Recommendations from the World Health Organization for influenza-like illnesses (ILIs) were used as the basis for influenza surveillance. If a patient presents with an acute cough and fever, clinicians must be highly vigilant to test for infections caused by the influenza virus. In general, the rate of ILI cases that lead to a clinical diagnosis of influenza infection is approximately 18 to 80%, which is higher than other clinical diagnoses, for example, acute infections of the upper respiratory tract [28]. We selected adult ILI patients for inclusion into the study. The study was designed to enroll 177 cases.

Specimen collection included pharyngeal/throat swabs and blood samples. Pharyngeal/throat secretions were obtained from the upper respiratory tract of each patient [29]. Pharyngeal/throat swabs will be used to test the mRNA of the influenza virus; the virus will be cultured. Blood samples will be used to test viral antibodies.

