#### Inclusion and exclusion criteria

Inclusion criteria are patients (i) with confirmed infection by the influenza A (H1N1, H3N2) or influenza B virus according to real-time polymerase chain reaction (PCR) or viral culture; (ii) aged 18 to 65 years; axillary temperature ≥38°C; at least two constitutional symptoms (headache, chill, myalgia or fatigue) and one respiratory symptom (cough, sore throat, or rhinitis) [30,31]; (iii) illness onset within 36 h; and (iv) granting of written informed consent. Exclusion criteria are detailed in Table 2.

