#### Rejection criteria and termination standards

Rejection criteria were (i) not meeting inclusion or exclusion criteria; (ii) withdrawal of informed consent; (iii) not receiving follow-up care after selection; or (iv) serious violation of the program (that is, incorrect administration leading to effects that cannot be judged).

Termination standards refer to patients who meet the inclusion criteria, but must be terminated during the trail and who are included in the final statistical analyses. Termination standards are detailed in Table 3.

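### No efficacy set is defined as all randomised patients by assigned arm; the main indicators sit in a completers-only per-protocol set with no clear lead set, and two virological confirmation rules conflict

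*Protocol article*

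**What the plan says.** **ITT.** The set "will include those patients who agree to enroll in the study and sign an informed consent form". Randomisation is not part of the definition. Table 1 places consent at the screening visit, beside the eligibility checks. No analysis is assigned to ITT anywhere in the article.

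**MITT.** The set "includes those patients who used the test drug at least once during randomization, and data will be used to indicate efficacy after intervention".

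**PP.** Members meet the inclusion criteria, follow the protocol with at most slight deviations, and complete both the trial and the case report form. "The PP is used to analyze the main indicators for evaluating efficacy"; the same sentence gives PP a second role, checking consistency with MITT. The Safety analysis population section again puts the main indicators in PP, adds that the MITT conclusion is evaluated too, and applies last observation carried forward within PP.

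**Removal and retention.** The rejection criteria include withdrawal of consent, "not receiving follow-up care after selection", and incorrect administration. The same section says that patients who meet the termination standards (Table 3) are part of the final statistical analyses.

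**Timing.** Under Data management, membership of all four sets is settled at data review, with unblinding after database lock.

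**Virology.** The Design section enrols on a rapid antigen test but says "if detection of nucleic acid of the influenza virus or cultivation of the influenza virus was inconsistent, the patient was excluded". The Inclusion and exclusion criteria section and Table 2 accept infection confirmed "according to real-time polymerase chain reaction (PCR) or viral culture".

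**The concern.** The Design section plans superiority over placebo and non-inferiority to oseltamivir. A superiority claim is protected by randomisation only if patients are compared as randomised. Here the set named ITT can include consented people who were never randomised and so have no arm. The set that carries the main indicators is selected on what happened after randomisation.

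That selection is related to outcome. Time to defervescence is a primary outcome, and Table 3 terminates patients for persistent high fever. Complications are a secondary outcome, and Table 3 terminates for pneumonia and for antibiotic treatment of secondary infection. A completers-only set therefore tends to lose treatment failures. If failures are more common on placebo, removing them shrinks a real benefit. If non-completion differs by arm for other reasons, it can create a benefit that does not exist.

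The virological conflict is a separate matter: it leaves open who belongs in the trial population at all.

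**Working it through.** **1. Is any efficacy set all randomised patients in their assigned arm?**

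| Set | Condition for membership | Role in the article |
|---|---|---|
| ITT | Signed consent, at screening | None stated |
| MITT | At least one dose, plus an unclear clause about efficacy data | Conclusion also evaluated |
| PP | Eligible, adherent, completed trial and case report form | Main efficacy indicators; consistency check on MITT |

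None is. The two sets used for efficacy are reported side by side, with no statement of which decides if they disagree.

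**2. Do the termination rule and PP fit together?** Rejection criteria and termination standards: terminated patients are in the final analyses. Per protocol population: members must complete the trial. Main indicators: placed in PP. These cannot all hold for the main efficacy analysis. They could be reconciled if MITT led and PP were secondary, but the article does not say so. Carrying observations forward within PP adds to the doubt, since members are supposed to have completed.

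**3. How large could the selection effect be?** The article gives no dropout rate, standard deviation (SD) or effect size, so this is an illustration under assumptions.

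- Inputs from the article: 177 patients ("The study was designed to enroll 177 cases") allocated 1:1:1, so 177/3 = 59 per arm; two-sided test at 0.05.
- Assumptions: the outcome is normal with SD 1 and there is no true effect. PP loses the slowest-recovering fraction q of one arm and a random fraction q of the other. This is a worst case: if the same kind of patient left both arms equally, there would be no bias under no effect.
- Bias = φ(c)/(1−q), with c the standard normal quantile at 1−q.
- Variance in the selected arm: v = 1 − c·φ(c)/(1−q) − [φ(c)/(1−q)]².
- SE = √[(1+v)/(59(1−q))]; b = bias/SE; false-rejection probability = Φ(b−1.96) + Φ(−b−1.96).

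For q = 0.10: c = 1.282 and φ(c) = 0.1755, so bias = 0.1755/0.90 = 0.195. Then v = 1 − 0.250 − 0.038 = 0.712, SE = √(1.712/53.1) = 0.180, b = 1.09, and the probability is about 0.19.

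| q | Bias (SD) | False-rejection probability |
|---|---|---|
| 0.05 | 0.11 | 9% |
| 0.10 | 0.20 | 19% |
| 0.20 | 0.35 | 48% |

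**4. The two virology rules.** Take a patient who is rapid-test positive, PCR positive and culture negative. Design: the culture disagrees, so on the natural reading the patient is excluded. Inclusion criteria and Table 2: PCR alone qualifies, so the patient is eligible.

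The number affected depends on culture yield s among PCR-positive patients, which the article does not give. If s is assumed to be 0.6 to 0.9, if all 177 are PCR positive and counted before exclusion, and if excluded patients are not replaced, the Design rule removes 177(1−s) = 71 down to 18 patients. It leaves 59s = 35 up to 53 per arm. The other rule removes none of them.

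**The case against.** Much can be said for the plan, and part of it stands.

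- **PP is not the only set.** A reader might infer that main efficacy rests on PP alone. The article does not support that: PP also checks consistency with MITT, and the MITT conclusion is evaluated. PP beside MITT is usual for non-inferiority. This stands; the defect is the missing lead set for superiority.
- **The sets are fixed blind.** A reader might infer that the population could be picked to suit the result. Under Data management, membership is settled before unblinding, which limits choice driven by arm. It does not help with selection on completion, because failures can differ by arm without anyone knowing the arm.
- **ITT is unused.** No comparison depends on its faulty definition. True, but this leaves the trial without the set that would protect randomisation.
- **MITT wording.** Reading it as requiring efficacy data, or as limited to the Ban-Lan-Gen (BLG) arm because that arm is called the test group, puts too much weight on garbled text. A near-identical clause appears in the safety set, and adverse events are compared between groups, so a BLG-only reading is implausible. This is a wording repair.
- **Virology.** The Design section does not say what a result must be inconsistent with. Exclusion on a pre-dose sample, judged blind, does not break randomisation. Both points stand: this is an eligibility contradiction only.
- **Pilot, condensed article.** The article calls the study a pilot, and fuller documents may exist. But the definitions and roles are stated here, and as stated they conflict.

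**Conclusion.** The point holds in a limited form. No efficacy set is all randomised patients by assigned arm, the main indicators are placed in a set conditioned on completion, and no lead set is fixed. The retention of terminated patients contradicts that completion requirement. For superiority over placebo this permits outcome-related selection in either direction. The possible bias of 0.11 to 0.35 SD is a worst case that assumes informative loss of 5% to 20% in one arm only; it is not a forecast.

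It would go too far to say that every set breaks randomisation. That description fits PP. It would fit MITT only if its unclear clause does require efficacy data, and it does not fit the virology rule. The 18 to 71 patients lost should not be quoted as an established figure. It rests on an assumed culture yield and on no replacement, whereas the abstract describes 177 recruited after meeting the criteria, including a positive virus test.

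**What to change.** Before unblinding:

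1. Define ITT as all randomised patients, analysed in the arm assigned.
2. Name one lead set for BLG versus placebo: either that ITT set, or all randomised patients with influenza confirmed on the pre-dose sample. In both cases keep withdrawn, terminated and non-adherent patients.
3. Make PP supportive for superiority and a second required set for non-inferiority.
4. Reconcile the retention of terminated patients with the completion requirement of PP.
5. Reconcile the Design section with the inclusion criteria and Table 2 into one confirmation rule, applied to the pre-dose sample.
6. In the set definitions, replace the reference to the test drug by any study medication.

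The changes are to definitions only. The article reports 50 patients finished by June 2014 and completion expected at the end of 2015, so on that timetable there was room to make them. The statistical price is a small dilution of the effect from keeping non-adherent patients.

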##### Safety analysis population

For the safety analysis population, data will demonstrate efficacy after intervention for those patients who use the test drug at least once during randomization. In this study, the baseline data, MITT analyses and main indicators for treatment are employed in PP analyses, but the conclusion from MITT analyses is also evaluated. When undertaking PP analyses, if there are missing data, the last observation carried forward (LOCF) approach will be adopted to complete the dataset. For laboratory data, adverse events and side effects, we will use SA analyses, and the SAP will be the denominator for the prevalence of adverse reactions.

#### Statistical analyses

The software used for statistical analyses will be SPSS v17.0 (IBM, Armonk, NY, USA) or SAS v9.2 (SAS Institute, Cary, NC, USA).

All statistical inferences will be determined using two-sided tests. *P* <0.05 will be considered significant, and 95% confidence intervals will be used.

Efficacy analyses will use LOCF to compensate for cases not fully covered during treatment. The LOCF approach uses the last data observed, which is transferred to the database to obtain a complete dataset. The safety assessment will not evaluate missing data.

A comparison between the dropout rate and dropout rate caused by adverse events will be undertaken using the Pearson’s χ^2^test.

Data will be described as the mean, standard deviation, and confidence intervals. If necessary, minimum, maximum, P25, P75, and median values will be provided. Paired measurement data will also show the differences between the mean and standard deviation. When using nonparametric methods, median and mean values will be provided. Count data will be described using the frequency distribution and corresponding percentage. Data of concentrations will be described using the frequency distribution and the corresponding percentage, as well as median and average values. Qualitative information will be described using the positive rate, the number of positive cases, and the denominator.

Baseline data analyses (two sets) will include demographic indicators, as well as general, primary and secondary indicators before intervention. Measurement data will be described using a *t*-test or t’ test (if the variance is absent). Count data will be described using the Pearson’s χ^2^test. Rating data will be described using the two-sample Wilcoxon rank sum test.

With respect to analyses of effectiveness, for quantitative variables, comparisons between groups will be undertaken using repeated measures analysis of variance and covariance analysis. For qualitative variables, comparisons between groups will be tested using the Pearson’s χ^2^test, whereas center effect analysis will use CMH. For rating variables, comparisons between groups will be tested using the Kruskal-Wallis test, regression analysis center effect via the CMH test, or grade logistics.

In terms of center effect analyses, the GLM method will be used for quantitative indicators and CMH methods for qualitative indicators. Rating variables will be evaluated and corrected using a logistic regression model.

With regard to subgroup analyses, depending on the circumstances, factors that cannot be excluded may have an effect on the prognosis.

For safety analyses, the prevalence of adverse events in the two groups will be compared using the Pearson’s χ^2^test, as well as listing and describing the events that occur during the trial. A description of laboratory test results before and after the test will be described as normal/abnormal changes, as well as the relationship between the abnormal changes and the test drug; these changes will be stated.

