### Study aims

Studies have suggested that BLG and its active ingredients may inhibit the influenza virus. Little concrete clinical evidence has been provided, however, for the efficacy of BLG in the treatment of seasonal influenza. We wished to evaluate the efficacy and safety of BLG granules for the treatment of seasonal influenza in an evidence-based clinical trial.

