### Safety and ethics

The drugs used in this clinical trial (BLG granules and oseltamivir) have been approved for clinical use, so there is no potential safety hazard. To ensure that study patients receive effective treatment during rehabilitation, the placebo control group will be provided basic drugs.

Before study commencement, we will explain in detail the research purpose, methods and processes. Satisfactory answers to any questions from the subjects, after obtaining written informed consent, will be included. Also, the center will focus on the purpose, application and execution of the study. Researchers will accept the research plan, treatment procedure, patients, research schedule, CRF and written informed consent. During the trial, the clinical unit must comply with GCP and the scheme of the clinical trial. Pharmaceutical supervisory and administrative departments will occasionally conduct audits and inspections and will cooperate with the sponsor to send medical examiners. Any moderate or serious adverse events will be reported to the Ethics Committee.

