## Discussion

Treatment effectiveness, safety assurance and patient affordability are the key factors for any drugs, including Western medicines and TCHMs. This projected clinical trial will provide evidence as to whether BLG granules are suitable and safe for treating and preventing seasonal influenza.

BLG seems to display a clinical effect during the early onset of illness. Our previous study showed that *IPRS*, clemastanin B and lignin, which are separated from *IIR*, have antiviral roles in the early infection stage of the influenza virus [24-26]. Accordingly, we defined the time of illness onset to be <36 hours. Unfortunately, this criterion made patient recruitment quite difficult. However, this design, which is based on a combination of traditional medical experience and modern pharmacological study, should allow us to discover the objective treatment effectiveness of BLG.

The safety of TCHM is attracting major attention. First, in our study, BLG granules are used only for 5 days in the acute phase, so that it may be safe for humans. Second, we evaluate the safety of BLG based on changes in liver and kidney function after treatment. In addition, western medicines used for treating influenza (such as oseltamivir, which sells for 283 RBM/box in China) is expensive for ‘developing’ countries. Hence, we need to explore new, safe and inexpensive anti-influenza medicine. BLG, which sells for 12.00 RBM/box in China, would be a good choice.

Furthermore, according to basic science studies, the active ingredient of *IIR* also exerts immune-modulating and anti-inflammation effects *in vitro* and *in vivo*. Polysaccharides from *IIR* can promote production of interleukin-2 and interferon-γ, as well as the proliferation of lymphocytes and macrophages in mice [33]. Also, indirubin and its derivatives can suppress the expression of several pro-inflammatory cytokines induced by influenza infection in human macrophages and alveolar epithelial cells [27]. Hence, an evidence-based clinical trial to evaluate the effectiveness of BLG in treating inflammation induced by influenza infection certainly has merit.

In summary, we have described the first clinical trial for treatment using a single herb against influenza A and B viruses in China. We will hold a large-scale clinical trial to comprehensively evaluate the effectiveness and safety of BLG against influenza infection based on the results of this pilot study.

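### The adverse-event test compares two unnamed groups in a three-arm trial, and at 59 per arm a non-significant result is weak evidence on whether BLG is safe

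*Protocol article*

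**What the plan says.** Study aims puts safety beside efficacy: "We wished to evaluate the efficacy and safety of BLG granules for the treatment of seasonal influenza in an evidence-based clinical trial". The Discussion promises a conclusion on it: "This projected clinical trial will provide evidence as to whether BLG granules are suitable and safe for treating and preventing seasonal influenza".

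The Design section describes three arms, "oseltamivir treatment (positive control), BLG granule treatment (test group) and placebo group", to which patients "were assigned randomly into three groups of equal proportions (1:1:1"). The section on number of participants gives the total: "The study was designed to enroll 177 cases".

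For adverse events, the Statistical analyses section says that "the prevalence of adverse events in the two groups will be compared using the Pearson’s χ^2^test", together with a listing and description of events. The general rule in that section is "All statistical inferences will be determined using two-sided tests", with significance at P<0.05. The same general paragraph says that 95% confidence intervals will be used, without naming the comparisons. The section on the safety analysis population makes that population the denominator for adverse reactions.

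The article states no expected adverse-event rate, no margin for excess harm and no power for the safety comparison.

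**The concern.** Two things are wrong with the sentence as it stands.

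First, it does not fit the design. A comparison of two groups in a three-arm trial leaves one arm out, and the text does not say which. The choice matters because the possible pairs answer different questions. BLG versus placebo isolates harm caused by BLG. BLG versus oseltamivir shows only whether BLG has more or fewer adverse events than an active drug which the Background itself describes as having side effects. If placebo is the arm left out, an excess common to both drugs cannot appear in the result.

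Second, the chi-square test is the only between-arm inference that the article describes for adverse events. A test of no difference can show harm if it rejects. If it does not reject, it leaves open how much harm remains possible. With 59 patients per arm and uncommon events, that range is wide.

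At stake is the quality of the safety evidence. The Discussion says a large-scale trial will be based on these results, so an interval for the excess risk would be more useful to its planners than a P value.

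**Working it through.** **Inputs from the article.** Total 177; three arms, 1:1:1; Pearson chi-square; two-sided; alpha 0.05.

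**Patients per arm.** 177/3 = 59. The article gives no basis for the 177 (no effect size, rate, margin or power), so that figure cannot be reproduced.

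**Assumption.** Adverse-event rates are not given. The comparator rate p is varied, and BLG is set at 2p.

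**1. Power to detect a doubling.** For x events on the comparator and y on BLG, with pooled proportion m = (x + y)/118, the uncorrected statistic is

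chi-square = ((y − x)/59)² / [m(1 − m) × 2/59],

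with rejection above 3.841. Power is the sum of Bin(x; 59, p) × Bin(y; 59, 2p) over all rejecting pairs (x, y).

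| Comparator vs BLG | Power | Doubling missed |
|---|---|---|
| 2% vs 4% | 7% | 93% |
| 5% vs 10% | 17% | 83% |
| 10% vs 20% | 34% | 66% |
| 15% vs 30% | 51% | 49% |
| 20% vs 40% | 67% | 33% |
| 25% vs 50% | 81% | 19% |
| 30% vs 60% | 92% | 8% |

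Check by normal approximation at 10% vs 20%: the null standard error is √(2 × 0.15 × 0.85/59) = 0.0657 and the alternative standard error is √((0.09 + 0.16)/59) = 0.0651. Power = Φ((0.10 − 1.96 × 0.0657)/0.0651) = Φ(−0.443) = 33%, in line with the exact 34%.

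Power crosses 50% at a comparator rate of about 15% and 80% at about 25%. A doubling is therefore missed more often than not only below about 15%.

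**2. Effect of the choice of pair.** Suppose BLG and oseltamivir both run at 20% and placebo at 10% (assumed). The same enumeration at 20% vs 20% gives rejection 5.3% of the time, so the BLG–oseltamivir test is non-significant about 95% of the time. BLG versus placebo (20% vs 10%) has 34% power. That is low, but it is the comparison in which the excess can appear.

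**3. What an interval would show.** Newcombe interval for the risk difference, built from Wilson limits for each arm.

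- Wilson limits: 6/59 = 10.2% (4.7% to 20.5%); 12/59 = 20.3% (12.0% to 32.3%).
- 12/59 on BLG vs 6/59 on placebo: the difference is 10.2 points. The lower limit is 10.2 − √((20.3 − 12.0)² + (20.5 − 10.2)²) = −3 points. The upper limit is 10.2 + √((32.3 − 20.3)² + (10.2 − 4.7)²) = +23 points. Chi-square = 2.36, P = 0.12.
- 6/59 in both arms: the difference is 0, with limits ±√((10.2 − 4.7)² + (20.5 − 10.2)²) = ±12 points.

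In the first case the P value alone would be reported as non-significant, whereas the interval shows that an excess of up to 23 percentage points has not been excluded.

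**The case against.** The strongest reply is that the article sets no rule by which P>0.05 means safe. A reader might infer one, since the chi-square is the only between-arm test described and the Safety and ethics section says that the study drugs "have been approved for clinical use, so there is no potential safety hazard". The documents do not support that inference. The ethics sentence rests on existing approval and governs no analysis. The Discussion's promise is neutral as to the answer. Safety is also to be judged from vital signs, electrocardiography, laboratory changes, causality grading and a listing of events. This part of the objection stands.

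A reader might also infer that a doubling of adverse events would usually go undetected. That is true only if the comparator rate is below about 15%, and the article gives no rate. At 25% or more the test has about 80% power or better.

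It can also be said that the general promise of 95% confidence intervals covers adverse events as much as the P<0.05 threshold does, and that a condensed article leaves such detail to the full plan. This is partly right: the intervals may well be intended. But the article does not attach them to the adverse-event comparison or say which contrast they would describe, and the two-group wording is a statement that conflicts with the design rather than an omitted detail. One could read it as each pairwise comparison in turn, but the text does not say so.

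Finally, the trial calls itself a pilot and leaves comprehensive safety evaluation to a later trial. That excuses low power. It does not settle which arms are compared, and a pilot is better served by estimates than by a test.

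**Conclusion.** The concern holds in a limited form. The adverse-event sentence contradicts the three-arm design and leaves the pair open. If that pair excludes placebo, harm from BLG that oseltamivir shares would not be seen. Separately, at 59 per arm a non-significant chi-square is weak evidence on safety when the comparator rate is below about 15% (83% missed at 5% vs 10%, 66% at 10% vs 20%), and less weak above it (33% missed at 20% vs 40%, 19% at 25% vs 50%).

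These figures rest on assumed event rates, full enrolment with all 59 patients per arm evaluable, and the uncorrected Pearson test. The sentence should be corrected, but it does not show that the trial would declare BLG safe on a null result.

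**What to change.** In the safety paragraph of Statistical analyses, replace the two-group comparison with wording such as: For adverse events in the safety analysis population, BLG will be compared with placebo (first) and with oseltamivir (second). For each contrast the risk difference will be reported with its two-sided 95% confidence interval (for example Newcombe), beside the Pearson chi-square test. The safety statement will rest on the upper confidence limit, the largest excess not ruled out by that interval, and not on P>0.05.

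This ties the confidence intervals already promised to named contrasts. It costs a few lines of text and a few intervals from data already collected, with no extra patients or visits. The downside is a less favourable safety statement: even with 6/59 in both arms, the upper limit would be about +12 percentage points.
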